## Methods

### Study Design

This study will use an explanatory sequential mixed methods design, combining quantitative and qualitative approaches to understand both implementation outcomes and contextual factors influencing intervention uptake [32]. The quantitative component will use a stepped-wedge approach across 4 health facilities (n=1899) [33,34] analyzed using generalized linear mixed models to account for clustering and repeated measures [34,35] with pre- and postassessment of implementation outcomes [36,37] (n=347; Figure 1). The qualitative component will involve thematic analysis of focus group discussions (FGDs; 5‐6 groups of ~6 key stakeholders) across 4 health facilities in Homa Bay County (Table 1). This analysis will combine deductive coding guided by Proctor’s implementation outcomes framework with inductive coding to capture emergent themes [36]. This integrated approach ensures rigorous evaluation of the Nishauri mHealth intervention across multiple levels and stakeholder perspectives.

**Figure 1. F1:**
[figure not shown]
Study Schema. FGD: focus group discussion; HCP: healthcare providers.

**Table 1. T1:** Focus group discussion (FGD) sampling plan or rationale.

Group	FGDs, n	Participants per FGD, n	Total participants, n	Plan or rationale
Men living with HIV	2‐3	6‐8	12‐24	Stratified by age, missed visits, antiretroviral therapy adherence, and intervention adoption.
Health care providers	2	6‐8	12‐16	Grouped by facility or role (eg, nurse vs adherence counselor). County or subcounty officials to provide valuable insight into policy, scale-up, and sustainability.
App developers	1	4‐6	4‐6	Being a homogeneous group, 1 FGD session should suffice.

After baseline data collection is completed, a standardized readiness assessment will be conducted across the 4 facilities to determine the procedure of the phased intervention rollout. We will leverage a partnership with the Palladium Group (the app developers) to access backend use data from the Nishauri app, providing detailed insights into how different app functions are used in real-world settings. This mixed methods design will enable both within- and between-facility comparisons, offering a nuanced understanding of how implementation processes and gendered experiences shape the intervention’s effectiveness among men. This study protocol was developed and reported in accordance with the SPIRIT (Standard Protocol Items: Recommendations for Interventional Trials) 2013 guidelines (Checklist 1).

### Study Setting

We will conduct this study in 4 subcounty HIV Comprehensive Care Clinics (CCC) in Homa Bay County, Kenya—Mbita, Ogongo, Ndhiwa, and Pala. Homa Bay County was chosen for its highest HIV prevalence, 16.2% [18] in Kenya, making it suitable to assess the implementation process and outcomes of an mHealth intervention for enhancing HIV care. The county covers an area of about 3154 km^2^ [38,39]. As of the 2019 Kenya National Census, it had an estimated population of approximately 1.1 million people [39]. There are approximately 160 health facilities providing HIV comprehensive care services across the county. ART uptake is at 96%, while viral load suppression (VLS) prevalence is at 83.8% among people living with HIV, with significant disparities between men and women [18,27,40].

The 4 health facilities have been selected based on feasibility factors such as patient volume and mobile network coverage, representativeness of diverse service delivery contexts, and requirements of the stepped-wedge design to ensure adequate clusters while minimizing contamination. They serve a total of 1899 men living with HIV aged 18‐55 years: Mbita (n=758), Ogongo (n=294), Ndhiwa (n=598), and Pala (n=249). The average distance between each neighboring facility is 25 km. Mbita and Ndhiwa subcounty hospitals are situated in an urban setup, while Ogongo and Pala subcounty health centers are located in relatively rural setups.

### About Nishauri mHealth Intervention

The Nishauri mHealth intervention is a client-centered digital platform developed by Palladium, in collaboration with Kenya’s Ministry of Health, and funded by the President’s Emergency Plan for AIDS Relief through the Centers for Disease Control and Prevention, to enhance HIV care and treatment outcomes. Nishauri supports key aspects of HIV care management, including appointment scheduling, ART referrals, and ongoing patient engagement. Its core functionalities include automated appointment and medication adherence reminders. It also enables tailored health education messages, 2-way communication between patients and health care providers, and behavior-change communication strategies to support retention in care. Patients with HIV using Nishauri can access their treatment engagement information and schedule or reschedule appointments through the app. A screenshot of the Nishauri app, captured directly from the live platform, is presented in Figure 2 for illustrative purposes.

**Figure 2. F2:**
[figure not shown]
Screenshot of the Nishauri mobile health app showing the home and dashboard interfaces.

Nishauri is the Ministry of Health–endorsed scale-up of Kenya’s earlier Ushauri system, which was piloted to support appointment reminders, treatment adherence messaging, and defaulter tracing through SMS, web, and mobile interfaces [19]. Building on the functionality and adoption of Ushauri, Nishauri is a client-centered mobile app that integrates in real time with the Kenya electronic medical record system and the Ushauri platform to support appointment scheduling, adherence reminders, 2-way communication, and behavior-change messaging for people living with HIV [19,20].

### Conceptual Framework and Theoretical Grounding

This study is guided by an integrated conceptual framework (Figure 3) drawing on Connell’s theory of hegemonic masculinity [29,41] and the TAM. Hegemonic masculinity provides a lens for understanding how dominant gender norms, such as expectations of strength, self-reliance, and economic provision, influence men’s engagement with HIV care and perceptions of digital health interventions. TAM informs the assessment of how perceived usefulness and ease of use of the Nishauri mHealth platform shape adoption and sustained use. These frameworks are integrated to examine how masculine norms modify technology acceptance and implementation outcomes, including adoption, acceptability, and engagement, ultimately influencing HIV care outcomes among men.

**Figure 3. F3:**
[figure not shown]
Study conceptual framework. ART: antiretroviral therapy; mHealth: mobile health; VLS: viral load suppression.

### Stepped-Wedge Intervention Approach

#### Strategy

A stepped-wedge design was chosen to allow all facilities to receive the intervention, accommodate phased training and app deployment, minimize contamination between sites, and enable within-facility comparisons over time while controlling for secular trends. The 4 CCCs will undergo a standardized readiness assessment, and phased implementation of the intervention will proceed in sequence according to facility readiness, with sites transitioning from standard care to the mHealth intervention arm over an 8-month period. The phased rollout will occur at 2-month intervals across the 4 participating facilities, resulting in 5 study periods (1 baseline and 4 intervention steps) over approximately 8 months. The 2-month interval was selected to align with routine HIV clinic visit schedules in Kenya [18], allow sufficient time for provider training and participant onboarding, and permit stabilization of app engagement before subsequent facility transitions. This interval is consistent with stepped-wedge evaluations of health service and digital interventions [42] and supports the detection of short-term changes in missed clinic visits and adherence behaviors while accounting for secular trends.

We acknowledge that the 2-month step length is relatively short and may limit detection of longer-term intervention effects within each wedge; however, this interval was selected for programmatic feasibility and alignment with routine HIV care cycles, and outcome measures were therefore chosen to capture proximal, short-term indicators of engagement and retention.

After baseline, all men who access HIV care from each facility will be trained on how to install and use the Nishauri app by adherence counselors or peer educators already trained by Palladium Group. This will happen during clinic education sessions as well as community outreaches organized through community ART (support) groups. Peer educators, through the community support groups, will provide follow-up support to ensure that all eligible men are reached. Contamination will be minimized by staggering rollout, restricting app activation to intervention sites, and monitoring cross-facility clinic attendance. We will track each participant’s primary facility at enrollment and confirm the facility where ART is routinely dispensed. Study inclusion will be restricted to men who are primarily engaged at 1 of the 4 participating facilities during the intervention period. Any participant who routinely receives care at multiple facilities will be carefully documented, and their data will be linked to the facility where they are primarily enrolled. These procedures are consistent with both national treatment guidelines and best practices for stepped-wedge designs in HIV implementation research.

Due to its facility-level implementation, individual-level exclusion criteria will not apply, as specified for the pre- and postassessment, which involves individual-level measurements and participant follow-up.

#### Outcomes

The primary clinical outcome will be missed clinic appointments, while secondary outcomes will include ART adherence (30-day percent visual analog), pharmacy refill consistency (medication possession ratio), and VLS—plasma HIV RNA <200 copies per milliliter. CCC data will be retrieved from facility electronic medical records and patient files, focusing on routinely collected HIV care indicators.

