#### Stepped-Wedge Analysis

We will analyze intervention effects using intention-to-treat principles and generalized linear mixed models appropriate to each outcome. Models will include a fixed effect for time period (step) to account for secular trends, a fixed indicator for intervention exposure during each step (within-cluster), and random intercepts for clusters (facilities) to account for within-cluster correlation. Where appropriate, we will include random slopes for time if supported by the data. Covariates prespecified for adjustment include patient-level baseline characteristics (age, gender, income, education, and stigma) and facility-level covariates (facility size and urban or rural). We will use robust SEs (cluster-robust SEs) to ensure valid inference with a limited number of clusters. Additional sensitivity analyses will include per-protocol analyses and models testing for time-by-intervention interaction to explore whether effect sizes change across steps. Primary inference will be 2-sided with *α*=.05. Analyses will be performed in Stata (StataCorp LLC; xtmelogit/xtmixed), and code will be archived with the study repository for reproducibility.

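### Secondary outcomes look back in time but exposure switches on at the step boundary with no lag, so first-exposed-step values partly measure control-period behaviour

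*Protocol article*

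**What the plan says.** The Strategy section sets the calendar: "The phased rollout will occur at 2-month intervals across the 4 participating facilities, resulting in 5 study periods (1 baseline and 4 intervention steps". It concedes that the step is short for longer-term effects and says that "outcome measures were therefore chosen to capture proximal, short-term indicators of engagement and retention".

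The Outcomes section names missed appointments as the primary clinical outcome. It then states that "secondary outcomes will include ART adherence (30-day percent visual analog), pharmacy refill consistency (medication possession ratio), and VLS", and that clinic data come from records, "focusing on routinely collected HIV care indicators". The only look-back length given is the 30 days of the adherence scale.

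The Stepped-Wedge Analysis section uses "generalized linear mixed models appropriate to each outcome", with a fixed effect for step and "a fixed indicator for intervention exposure during each step (within-cluster". It names no lag, washout or transition step. The nearest safeguard is a sensitivity model with a time-by-intervention interaction.

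Two other places bear on the adherence scale. Quantitative Data Collection and Storage puts survey data at baseline and at 8 months. Limitations counts adherence among the self-reported survey measures.

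**The concern.** The exposure indicator changes on a calendar date, but the secondary measures do not change with it. A 30-day recall taken 10 days after go-live covers 20 days before it. Possession early in the first exposed step rests on drug collected before go-live. A viral load drawn shortly after go-live reflects earlier pill-taking. Coded as written, control-period behaviour enters the model as exposed behaviour.

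The bias runs toward no effect. It also falls on the cells that matter most, because in a four-facility wedge with period effects the contrast is identified almost entirely from each facility's first exposed step. A real improvement in adherence, possession or suppression could be reported as small or absent. The Discussion treats suppression as a downstream sign of possible clinical impact, so its null result is the one most open to misreading.

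**Working it through.** **Inputs from the article.** Step length 2 months, taken as 60 days (Strategy). Adherence look-back 30 days (Outcomes). Facility sizes 758, 294, 598 and 249, total 1899; 5 periods; control proportion 0.20; odds ratio 0.75; intracluster correlation 0.02 (Power Estimation for Stepped Wedge Analysis).

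**Assumed.** Refill intervals of 1, 2, 3 and 6 months, since none is stated. The 2-month case follows the Strategy section's visit cycle, if refills follow visits. Assessments and refill dates are spread evenly relative to go-live, and the full effect starts at go-live.

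**The plan's own figure.** No power is stated for a secondary outcome. The stated power of about 80% for missed visits reproduces under a Hussey-Hughes layout: 81% analytically (79% to 84% by rollout order) and 81% by simulation, with all 1899 men observed in every period. The layout is therefore read correctly.

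**Control share of the first exposed step.** For a look-back of w days in a 60-day step, the mean share before go-live is w/120 if w ≤ 60, and 1 − 30/w otherwise.

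- 30-day scale: 30/120 = 25%. Records touching control time: 30/60 = 50%. If all are collected at step end: 0%.
- Possession: residual supply at go-live is uniform on (0, R), so the mean number of the 60 days covered by earlier refills is R/2 for R ≤ 60, and 60 − 1800/R otherwise.

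| Refill interval | Days from earlier refills | Share of 60 |
|---|---|---|
| 30 days | 15 | 25% |
| 60 days | 30 | 50% |
| 90 days | 60 − 20 = 40 | 67% |
| 180 days | 60 − 10 = 50 | 83% |

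**Weight on those cells.** With four equal facilities, the generalized least squares weights on the first exposed cells are 0.300, 0.264, 0.229 and 0.193, summing to 0.986. With the actual sizes over all 24 rollout orders, the sum averages about 0.99 (0.93 to 1.05). These are 4 of the 10 exposed cells. The other six nearly cancel.

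**Share of the true effect recovered** (actual sizes, averaged over rollout orders). With equal facilities and windows up to 60 days this is 1 − 0.986 × control share: 1 − 0.986 × 0.25 = 0.75 and 1 − 0.986 × 0.50 = 0.51. Longer windows also dilute later steps.

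| Window or refill interval | Effect recovered |
|---|---|
| 30 days | 0.75 |
| 60 days | 0.51 |
| 90 days | 0.32 |
| 180 days | 0.04 |

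The weights come from a linear exchangeable model, so they are indicative for logistic outcomes.

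**If the adherence scale is only a survey item.** Go-live falls at about months 0, 2, 4 and 6. At the 8-month survey the last facility has been live about 2 months, which exceeds 30 days, so no recall window crosses go-live at any facility.

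**Cost of leaving values out.** Halving the numbers in the four first-exposed cells and recomputing the generalized least squares variance raises the standard error by about 13% (11% to 15% by rollout order).

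**The case against.** The strongest reply is that much of this turns on details a journal article may leave to the full protocol or analysis plan: the possession window, refill and testing intervals, and the rule placing a result in a step. That stands. Their absence is not the point, and the article does not say that viral loads are carried forward. What the article does fix is the exposure coding and the kind of outcome, and those two do not fit together without a lag.

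A second reply is that intention-to-treat makes onset dilution part of the rollout effect. That is fair for slow uptake after go-live. It does not cover days before go-live. The time-by-intervention model might show a smaller early effect, but it does not reassign those days.

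Some stronger readings are tempting and are not supported:

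- A reader might infer that most of the first exposed step is control behaviour for all three outcomes. For the only stated window the mean share is 25%, and half of the records are affected only in part. The larger figures rest on assumed intervals.
- A reader might take it as settled that the adherence scale is measured at every step. The survey schedule and the Limitations section leave open that it is not, and in that case nothing crosses go-live.
- Sparse routine viral load testing within a step would be a question of data volume. It does not measure look-back.
- That the last facility has one exposed step is the ordinary stepped-wedge layout. It does not follow that suppression must be reported only descriptively.
- The Strategy rationale and the Discussion's description of suppression as downstream sit awkwardly together, but this is a matter of wording and no proof that a null would be misread.

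**Conclusion.** The concern holds in limited form. With exposure coded by step and no lag, the first exposed step mixes control and exposed time for the secondary outcomes, biasing their effects toward zero. Later steps do not repair this, because about 0.99 of the net weight lies on the first exposed cells.

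For the 30-day scale, the estimated effect shrinks by about a quarter if it is collected evenly through each step, and not at all if it is collected at step end or only at 8 months. For possession, the loss is about half if refills follow a 2-month cycle, and anywhere from a quarter to nearly all of the effect over the assumed 1- to 6-month range. For viral load, the direction is clear but the documents do not allow a size. All of these figures assume even timing and an immediate full effect. Missed appointments and the associated power statement are not touched. The point is worth acting on, but it is not a threat to the trial's main conclusion.

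**What to change.** For the secondary outcomes, assign exposure by look-back window:

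- compute possession from the first refill due after go-live;
- count a 30-day recall as exposed only if taken at least 30 days after go-live;
- use viral loads by sample date, without carry-forward, leaving out those drawn within a prespecified interval after go-live.

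Alternatively, treat the first exposed step as a transition in a sensitivity analysis.

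State whether the adherence scale is collected at every step or only at baseline and 8 months, and reconcile Outcomes, Stepped-Wedge Analysis, Quantitative Data Collection and Storage, and Limitations on this. If it is collected only twice, the by-step model as described cannot be applied to it. Reconcile the short-term rationale in Strategy with including suppression, and say that a null suppression result will be interpreted in light of the short exposure.

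The change is one of wording, and it uses refill and sample dates that should be in the same routine records. The price is fewer first-step values: about 13% on the standard error if half of them are left out, and more if a larger share goes. That matters because those cells carry most of the information.

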#### Implementation Outcomes

Guided by Proctor’s implementation outcomes framework, this study seeks to evaluate multiple implementation outcomes of the Nishauri mHealth intervention using a mixed methods approach. The primary implementation outcome will be adoption. Adoption will be measured as completion of app installation and account activation within 60 days of introduction. Acceptability (the perceived satisfaction and appropriateness of the intervention among users and providers) and use will be assessed through validated survey instruments, including the System Usability Scale and intervention acceptability measures, alongside qualitative data from FGDs with users and providers. Early indicators of sustainment are assessed through continued engagement metrics over the study period and stakeholder perspectives on long-term integration and scalability, acknowledging that full sustainment extends beyond the study time frame.

#### Stepped-Wedge Analysis

We will analyze intervention effects using intention-to-treat principles and generalized linear mixed models appropriate to each outcome. Models will include a fixed effect for time period (step) to account for secular trends, a fixed indicator for intervention exposure during each step (within-cluster), and random intercepts for clusters (facilities) to account for within-cluster correlation. Where appropriate, we will include random slopes for time if supported by the data. Covariates prespecified for adjustment include patient-level baseline characteristics (age, gender, income, education, and stigma) and facility-level covariates (facility size and urban or rural). We will use robust SEs (cluster-robust SEs) to ensure valid inference with a limited number of clusters. Additional sensitivity analyses will include per-protocol analyses and models testing for time-by-intervention interaction to explore whether effect sizes change across steps. Primary inference will be 2-sided with *α*=.05. Analyses will be performed in Stata (StataCorp LLC; xtmelogit/xtmixed), and code will be archived with the study repository for reproducibility.

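### The on/off exposure term makes the stepped-wedge estimate essentially an effect of each site's first 2 months, and no planned analysis clearly shows the effect by time since rollout

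*Protocol article*

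**What the plan says.** All references are to the Methods of the protocol article.

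- **Stepped-Wedge Analysis.** On time: "Models will include a fixed effect for time period (step) to account for secular trends". On treatment: "a fixed indicator for intervention exposure during each step (within-cluster". Facilities have random intercepts. The stated model has no transition period and no term for time since a site's rollout.
- **Same section, sensitivity analyses.** These include "models testing for time-by-intervention interaction to explore whether effect sizes change across steps".
- **Strategy (layout).** Sites cross over one at a time, every 2 months. The section describes this as "resulting in 5 study periods (1 baseline and 4 intervention steps) over approximately 8 months".
- **Strategy (purpose of the interval).** It is meant to "allow sufficient time for provider training and participant onboarding, and permit stabilization of app engagement before subsequent facility transitions". The same section says the interval supports detecting short-term changes in missed visits and adherence, and concedes that longer-term effects may be missed within a step.
- **Implementation Outcomes.** "Adoption will be measured as completion of app installation and account activation within 60 days of introduction". Sixty days is about one step.
- **Power Estimation for Stepped Wedge Analysis.** About 80% power for an odds ratio of 0.75 under a Hussey-Hughes model, with a missed-appointment proportion of 0.20, an intracluster correlation (ICC) of 0.02 and 1899 men. That model takes the effect as immediate and constant.

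**The concern.** A single on/off term is easily read as an average over all exposed time. In a stepped-wedge layout with period effects it is not. The later exposed cells of early sites also act as comparison cells for the sites that cross over later, so their weight can be small or negative. With one facility per step and a 2-month step, the estimate may then rest on the weeks in which men are still being trained and are installing the app.

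At stake is how the main result is read. If benefit builds up after onboarding, the odds ratio could sit near 1 although the established app works, and benefit gained in months 5-8 would push the estimate the wrong way. A reader would have nothing in the planned output to reveal this.

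**Working it through.** **Inputs.** Facility sizes 758, 294, 598 and 249; proportion 0.20; ICC 0.02; odds ratio 0.75; two-sided alpha 0.05; 5 periods with one facility crossing per step. Rollout order depends on readiness and is not fixed, so all 24 orders were used. Assumption: each man contributes one observation in every period.

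**Step 1: the plan's own power.** Odds 0.25 × 0.75 = 0.1875, so the exposed proportion is 0.1875/1.1875 = 0.158, a difference of 4.21 percentage points. Generalized least squares with total variance 0.20 × 0.80 = 0.16 gives a mean standard error of 1.53 points. Power is Φ(4.21/1.53 − 1.96) = Φ(0.79), about 79% (76-81% over the orders). A logistic check gives 81% (78-83%). The stated figure of about 80% reproduces for an immediate, constant effect.

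**Step 2: the weights.** The estimate is a linear combination of the 20 facility-period means, Σ c(i,j)·y(i,j). If the true effect in exposure period s is δ(s), its expectation is Σ W(s)·δ(s), where W(s) sums c(i,j) over the cells in their s-th exposed period.

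| Time since rollout | Mean weight | Range over 24 orders |
|---|---|---|
| Months 1-2 | 0.99 | 0.93 to 1.05 |
| Months 3-4 | 0.30 | 0.22 to 0.42 |
| Months 5-6 | -0.09 | -0.17 to 0.02 |
| Months 7-8 | -0.19 | -0.29 to -0.11 |

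For ICC 0.01 to 0.05 the first weight stays within 0.92-1.06.

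**Step 3: a hand check.** Take equal facilities and facility effects removed entirely. The weight of a cell is then proportional to exposure − facility mean − period mean + 0.5. Facility i (1 to 4) has mean (5−i)/5; the five period means are 0, 1/4, 1/2, 3/4 and 1.
- First exposed period: 0.5 − 0.05i, summing to 1.50 over i = 1-4.
- Second: 0.25 − 0.05i, summing to 0.45 over i = 1-3.
- Third: −0.05i, summing to −0.15 over i = 1-2.
- Fourth: −0.25 − 0.05 = −0.30.

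The total is 1.50, so the weights are 1.0, 0.3, −0.1 and −0.2. The pattern comes from the layout.

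**Step 4: what the model recovers.** Multiply the weights by an assumed effect pattern to get the recovered share r. Power for a significant result in favour of the app is Φ(r × 4.21/1.53 − 1.96), averaged over orders.

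| Effect in exposure periods 1, 2, 3, 4 (share of full) | Recovered | Power at full OR 0.75 |
|---|---|---|
| 1, 1, 1, 1 | 100% | 79% |
| 0.8, 1, 1, 1 | 80% | 60% |
| 0.5, 1, 1, 1 | 51% (48-54%) | 29% |
| 0.25, 1, 1, 1 | 26% | 11% |
| 0, 1, 1, 1 | 1% (-5 to 7%) | 3% |
| 0.25, 0.5, 0.75, 1 | 13% (10-17%) | 6% |

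For the last row the true four-period average is 62.5%.

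**Step 5: 0/0.5/1 coding.** Scoring the first exposed period as 0.5 gives mean weights 0.00, 1.08, 0.13 and -0.22. It recovers 100% of any pattern that is flat from month 3 and 42% of the linear ramp. The zero holds only for the sum over sites: single first-period cells carry weights of up to 0.24 in absolute value. Power for an immediate effect is 50%.

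**Step 6: pre-rollout periods.** With six pre-rollout periods in all (the planned baseline plus five more):

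| True pattern | Power, on/off | Power, 0/0.5/1 |
|---|---|---|
| Immediate | 88% | 70% |
| Half effect in first period | 51% | 70% |

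**The case against.** **The first period is also an evaluation window.** A reader might infer that the plan reserves each site's first 2 months for onboarding. It does not: the Strategy section also expects short-term changes there, and 60 days is a ceiling for counting adoption, not evidence that nothing happens earlier. This stands.

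**The loss is conditional.** A reader might infer that any delayed benefit is cut by half or more, or would probably be reported as null. That needs a first-period effect of about half or less. With 80% the loss is 20%. Even with 50%, the loss against the four-period average (0.875) is 39-46%. The article gives no uptake curve, so no single loss can be asserted. This stands too.

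**An effect that includes roll-in is a legitimate intention-to-treat target.** Agreed. The weights are a different matter: intention to treat governs who is analysed, and does not imply near-zero or negative weight on months 5-8.

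**The plan already probes changing effects.** The interaction is worded across steps, which most naturally means calendar step, and it leaves the primary estimate unchanged. The concession about longer-term effects concerns step length, not weighting. The planned per-protocol analyses, and the training and installation dates to be collected, help interpretation but do not alter the weights either.

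**The weights depend on the model.** The Abstract names generalized estimating equations. With an independence working correlation and equal facilities the weights are 0.6, 0.3, 0.1 and 0. None is negative, and a half-effect first period loses 30%, but the first period still dominates, and the 0, 1, 1, 1 pattern is recovered at 40%. Random slopes, if used, would change the weights as well.

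**Conclusion.** The point holds as one about weighting and labelling. Under the stated primary model, the odds ratio is essentially the effect in each site's first 2 months, with a first-period weight of 0.93-1.05 whatever the rollout order at ICC 0.02. The planned output has nothing that clearly separates effects by time since rollout. How much is lost depends on an uptake pattern that the documents do not give: from nothing if the effect is immediate, through about half if the first period delivers half, to nearly all if it delivers none.

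A reader might also infer that the primary coding should be replaced by 0/0.5/1. The figures do not support that as a plain correction. It moves the weight to months 3-4, keeps a negative weight on months 7-8, and cuts power from 79% to 50% if the effect is immediate. It is a trade-off.

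Assumptions: the Hussey-Hughes variance, one observation per man per period, and a normal-based test with only 4 facilities. If instead the 1899 men were spread over the 5 periods, power would be about 24%, but the first-period weight would still be 0.89-1.00.

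**What to change.** 1. Replace the calendar-step interaction with a prespecified model that gives a separate effect for each exposure period 1 to 4 since crossover, reported next to the primary estimate.
2. Keep the on/off model as primary. Label its odds ratio as including, and dominated by, the roll-in period, and state that a null result will not be read as no effect of the established app.
3. Add 0/0.5/1 coding of the first exposed period as a sensitivity analysis. State that it estimates the post-onboarding effect only if that effect is flat from month 3 and the first-period effect is similar across sites.
4. Where routine records exist, add pre-rollout periods to all of these models, not only to the new coding.

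**Cost.** Changes of wording, some extra analysis and extraction of earlier records. The period-specific estimates will be imprecise: without extra periods the standard errors are about 1.67 points for the first exposed period and 2.23 for the second, and power for the average of the four periods at an odds ratio of 0.75 is about 41%. They should be presented as descriptive. Follow-up is already under way in the first facility, so the wording should be settled before outcome data are analysed.
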